							**Phone follow-up**	
			**Anamnestic evaluation**	**Baseline evaluation**	**3 months from T0**	**6 months from T0**	**12 months from onset**	**24 months from onset**
		Etiology		X				
		Brain localization and extension		X				
		Trial of Org 10172 in Acute Stroke Treatment		X				
**Acute event**		Oxfordshire Community Stroke Project		X				
		Early clinical complications		X				
		Treatment received during the acute phase (thrombolysis/fibrinolysis)		X				
		Procedure complications		X				
		Cumulative Illness Rating Scale	X	X	X	X		
		Presence of medical device		X	X	X	X	X
**Clinical complexity**		Body mass index	X	X	X	X	X	X
		Braden scale		X	X	X		
		Relevant medical complications				X	X	
		Pain assessment (NRS/NCS/PAINAD)		X	X	X		
	**Consciousness**	Glasgow Coma Scale		X				
		Coma Recovery Scale revised		X	X	X	X	X
	**Neurocognitive evaluation**	Cognitive reserve index	X					
		Level of cognitive functioning		X	X	X		
**Functional assessment**		Galveston Orientation and Amnesia Test			X	X		
		Apathy Evaluation Scale			X	X		
		Agitated Behavior Scale			X	X		
		Halpern communication scale or the Goodglass–Kaplan communication scale			X	X		
		Montreal cognitive assessment					X	X
	**Sensorimotor assessment**	Trunk Control Test	X	X	X	X		
		Modified Ashworth scale		X	X	X		
		Functional Oral Intake Scale		X	X	X	X	X
	**Disability level**	Early rehabilitation Barthel Index	X	X	X	X		
		Disability Rating Scale		X	X	X		
		Functional improvement measure		X	X	X		
		Glasgow Outcome Scale-expanded	X	X	X	X	X	X
	**Participation level**	Community I Questionnaire					X	X
		Electroencephalography		X	X			
**Neurophysiological evaluation**		Somatosensitive Evoked potential		X				
		Motor-evoked potential		X	X			
		Electromyography		X	X			
		ApoE		X	X	X		
**Genetic markers**		Brain-derived neurotrophic factor		X	X	X		
		Dopamine receptor 2		X	X	X		

***Legend:** Clinical complications: metabolic, cardiovascular, muscular and skin, gastrointestinal, genitourinary, respiratory, epilepsy or myoclonus, neurosurgery compliances, POA, PHS*.

#### Neurophysiological Assessment

Neurophysiological evaluations will be performed within 1 week after the IRU admission. In case of the availability of SEP recorded in the acute–subacute setting, the examination will not be repeated.

##### EEG (At T0 and T1)

An EEG of 30 min of wakefulness will be performed using Galileo NT (EBNEUR) with 32 channels through an EEG prewired headcap with 19 recording electrodes, one ground electrode, and a reference positioned according to the 10–20 international system. The signal will be sampled at 128 Hz, and the sensitivity will be set at 7 μV/mm and then filtered (1.6–30 Hz). The examination will be carried out on a bed or a wheelchair based on the patient's clinical conditions. During the 30-min recording period, patient reactivity will be assessed through active or passive eyes opening and closing, depending on the degree of patient collaboration, and through acoustic and nociceptive stimuli, each stimulus repeated three times.

The EEGs will be classified according to the ACNS terminology (28); the EEG descriptors taken into account will be continuity, voltage, frequency, reorganization of an anterior or posterior gradient of the background activity, symmetry, the presence of spontaneous variability, the presence of reactivity of the background activity, and the presence of epileptic discharges and detectable EEG stage II sleep patterns. Additionally, epileptiform abnormalities will be classified as follows: (1) interictal epileptiform activity, (2) periodic discharges, and (3) electrographic seizures.

##### Somatosensory-Evoked Potential (T0)

Right and left median nerves will be stimulated at the wrist by a bipolar surface electrode, at an intensity of 4–5 mA, greater than the one needed to evoke a muscular response from abductor pollicis brevis, with a pulse duration of 0.2 ms and stimulus rate at 3 Hz. Recordingstainless steel needle electrodes will be placed at different locations to ensure recording of peripheral, spinal, bulbar, and cortical components. The locations to consider will be the following: Erb's point (referred to contralateral Erb's point), spinous process CV7 (referred to the anterior neck), and C3 and C4 (referred to Fz and ipsilateral mastoid). At least two repetitions (averages of 300 responses) will be acquired to assess the reproducibility of waveforms. The analysis time will be 100 ms, with a bandwidth of 5 Hz−3 kHz. The N20 wave will be identified as the major negative peak with a latency of approximately 20 ms from the stimulus, whereas P25 will be identified as the major positive peak following N20. Considering the cortical responses of each hemisphere, we will obtain six SEP patterns: *NN-NP-PP-NA-AP-AA*. *N* will stand for normal (N20/P25 amplitude is normal); *P* will stand for pathological (N20/P25 amplitude <1.2 μV); *A* will stand for N20 absence (if no reproducible components will be identified in the presence of a cervical potential) (29).

##### Motor-Evoked Potentials (T0)

Transcranial magnetic stimulation (TMS) will be performed according to the standard criteria of the International Federation of Clinical Neurophysiology (30). Motor-evoked potentials (MEPs) will be recorded from abductor digiti minimi (ADM) and tibialis anterior (TA) muscles. Exclusion criteria are (1) the presence of pacemaker, (2) the presence of physical limitations (e.g., bandages or plasters) that prevent the evaluation of peripheral muscular response through the compound muscle action potential (CMAP), and (3) the presence of craniotomy.

The examination will be conducted with the Medelec Synergy electromyograph (Natus Europe) associated with the MagVenture MagPro Compact magnetic stimulator equipped with a circular coil. Disposable surface electrodes (BionenFlorence, Italy) will be placed on the muscle under examination. Once the motor response of supramaximal amplitude will be obtained, the magnetic stimulus will be delivered. A circular coil will be used to map the area of interest corresponding to the target muscles studied. For the TA, given the cortical representation, the coil will be positioned slightly ipsilateral to the side under examination in correspondence to Cz, whereas for the ADM, the coil will be positioned contralateral, taking Cz as reference. The stimulus will be delivered in a resting situation because of the low level of patient consciousness. A stimulus will be provided at the paraspinal level only in the assessment of the upper limbs due to the increased accessibility of the stimulation site.

The MEP will be classified as follows:

Normal.Pathological if the MEP will be recordable but not within the reference values for amplitude and/or absolute latencies.Absent if the potential amplitude will be <50 μV could be obtained after 5 stimuli at 100% intensity.

##### Electroneurography/Electromyography (T0)

The electroneurography/electromyography (ENG/EMG) will be performed using a MEDELEC Synergy Oxford device. All patients will undergo conventional orthodromic motor and antidromic sensory nerve conduction studies on eight motor nerves (axillary, ulnar, common peroneal, and tibial nerves, bilaterally) and four sensory nerves (ulnar and sural nerves, bilaterally). The muscular activity will be assessed with concentric needle electrodes at rest and, when possible, during contraction. Sensory nerve action potential (SNAP), distal motor latencies, CMAP, and nerve conduction velocities will be registered. Spontaneous activity and, when possible, recruitment and interference patterns will be detected bilaterally by needle EMG from deltoid, ADM, and tibial anterior muscles. Patients with conduction velocities <20% of the lower limit will be diagnosed as having possible polyneuropathy of other causes and will be excluded from the analysis.

For conduction velocities, normal limits will be defined as mean ± 2 standard deviations (SDs) of normative data of our laboratory. For CMAP and SNAP, the lower limit will be set to the 5th percentile derived from the normative data of our laboratory (31).

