On the other hand, only a few studies have investigated the clinical conditions in patients with prolonged DoC in the long term (8, 9, 11). As the evidence about functional and clinical conditions of these patients in the middle- and long-term is limited, a consensus about solid predictors of recovery is still missing.

More recently, a higher total score on the Coma Recovery Scale-revised (CRS-R) at admission in the intensive rehabilitation unit (IRU) and the progression of this score during the first 4 weeks of hospitalization have been identified as prognostic factors for consciousness or responsiveness recovery in the medium-term (12, 13). Moreover, for what concerns quantitative measures, the bilateral absence of cortical (N20) components of somatosensory-evoked potentials (SEPs) is considered the most accurate neurophysiological marker for an unfavorable prognosis of consciousness improvement with high specificity, especially in the postanoxic etiology of DoC, for both short- (14) and long-term prognoses (15, 16). Further, visual analysis of conventional EEG background activity and reactivity collected upon admission to the IRU was recently identified as a possible predictive marker for a better evolution of consciousness at discharge (17–19) or 6 months after brain injury (20). Additional factors have been reported to be prospectively associated with motor improvement in sABI patients who recovered consciousness: the evaluation of residual central neural motor circuit and the analysis of motor-evoked potential (MEP) may increase prognostic accuracy for motor limb recovery and thus improve the functional prognosis in brain-damaged patients (21). Further, the presence of critical illness neuromyopathy (CINMP), diagnosed by electromyography at the IRU admission, has been reported to associate with a lower functional outcome at discharge (18, 22).

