The personalization of rehabilitation strategies is yet largely bounded by the limited knowledge existing on biomarkers of rehabilitation outcome. Thus, besides the clinical–functional component, this study will also investigate neurophysiological and genetic parameters as possible biomarkers of functional outcome. In addition to neurophysiological examinations, to improve the diagnosis of causes of impaired consciousness, the former can make a valuable contribution in assessing subsequent outcomes such as functional autonomy (including both motor and cognitive influence) and the degree of participation. As to motor recovery, it will be verified whether and how the combination of the collected neurophysiological measures (ENG/EMG and MEP) could contribute to the motor prognosis. Recent studies have emphasized the importance of some neurophysiological markers as possible predictors of motor recovery after vascular brain injuries (21). Namely, an ipsilesional loss of power in the alpha frequency band and an increase in the delta frequency band in the EEG, detected within 2 weeks of brain vascular damage, are linked to a poor outcome (53). Moreover, the presence of CIPNM in sABI patients was found to be related to reduced functional recovery and longer time to tracheostomy decannulation (22). The EEG, in addition to the identification of epileptic abnormalities as a possible predictive index of the remote structural epilepsy (SE) occurrence, could provide data for quantitative analysis (connectome) for the eventual prediction of SE onset during the IRU stay and after it. Indeed, the prevalence of SE after sABI was estimated at 16.4% (54), and posttraumatic sABI patients are more likely to develop SE (51). The SE could hamper recovery of consciousness in patients with prolonged DoC (55) and increase mortality in patients with vascular sABI (56).

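### The nerve-conduction exclusion threshold, read as written, is one fifth of the lower limit; a plausible other reading is four times higher, and the protocol does not say which is meant

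*Protocol article*

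**What the plan says.** Under Electroneurography/Electromyography (T0), the protocol article lists the nerves to be tested, "eight motor nerves (axillary, ulnar, common peroneal, and tibial nerves, bilaterally) and four sensory nerves (ulnar and sural nerves, bilaterally"), and then sets a rule that both labels patients and removes them: "Patients with conduction velocities <20% of the lower limit will be diagnosed as having possible polyneuropathy of other causes and will be excluded". The sentence goes on to say that such patients leave the analysis, without naming which one. The reference limit follows: "For conduction velocities, normal limits will be defined as mean ± 2 standard deviations (SDs) of normative data of our laboratory". No value in m/s is given, and the threshold is not restated elsewhere.

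Three other sections bear on the rule:

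- **Statistical Analysis** makes neurophysiological parameters one of the predictor categories entered into logistic regression for the primary outcome (GOS-E above 4).
- **Discussion** commits the study to verifying "whether and how the combination of the collected neurophysiological measures (ENG/EMG and MEP) could contribute to the motor prognosis".
- **Study Design and Participants** says that nothing beyond missing consent, or age or time from onset out of range, excludes a patient.

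The Introduction gives the clinical background: "the presence of critical illness neuromyopathy (CINMP), diagnosed by electromyography at the IRU admission, has been reported to associate with a lower functional outcome", as measured when patients leave the unit.

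**The concern.** A rule that labels a patient as having possible polyneuropathy should respond to conduction that is clearly slower than the laboratory's limit. As worded, it responds only when velocity has fallen to less than one fifth of that limit. The phrase could be a slip for a reduction of more than 20% below the limit, but the text does not say so.

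The threshold decides who contributes to the ENG/EMG analyses. If it is applied as written, patients with marked slowing are kept. If it is applied on the other reading, some of those patients are removed. In either case a reader of the results could not tell from this text which rule had been used. The four units are meant to collect data homogeneously, and a threshold open to two readings does not serve that aim.

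**Working it through.** There is no sample-size or power figure to reproduce here. The check is what the stated threshold means relative to the limit the section itself defines.

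**Inputs from the document**
- Lower limit for conduction velocity: LLN = mean − 2 SD of laboratory norms (ENG/EMG section).
- Threshold: below 20% of that limit (same section).

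**Assumption, not in the document**
- c = SD/mean of the normative velocities, taken from 0.05 to 0.20.

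**Step 1: the two readings as fractions of the limit**
- Fraction of the limit (literal): cut-off = 0.20 × LLN.
- Reduction below the limit: cut-off = (1 − 0.20) × LLN = 0.80 × LLN.
- Ratio: 0.80 / 0.20 = 4, independent of the norms.

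**Step 2: distance below the normative mean, in SD units**

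With LLN/mean = 1 − 2c:
- Literal: [1 − 0.20(1 − 2c)] / c = 0.8/c + 0.4.
- Reduction: [1 − 0.80(1 − 2c)] / c = 0.2/c + 1.6.

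| c | literal cut-off as % of mean | literal, SD below mean | reduction reading, SD below mean |
|---|---|---|---|
| 0.05 | 18.0 | 16.4 | 5.6 |
| 0.08 | 16.8 | 10.4 | 4.1 |
| 0.10 | 16.0 | 8.4 | 3.6 |
| 0.15 | 14.0 | 5.7 | 2.9 |
| 0.20 | 12.0 | 4.4 | 2.6 |

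The lower limit itself is 2 SD below the mean in every row.

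**Step 3: which patients are classified differently**

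Let r be a patient's velocity divided by the limit.
- r below 0.20: flagged on both readings.
- r from 0.20 to just under 0.80: flagged only on the reduction reading.
- r of 0.80 or more: flagged on neither.

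The readings therefore disagree for every patient slowed by more than 20% and up to 80% below the limit. A velocity at half the limit (r = 0.50) is kept as written and excluded on the other reading.

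**Step 4: illustration in m/s (limits assumed)**

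For limits of 35, 40, 45 and 50 m/s, the literal cut-off is 7, 8, 9 and 10 m/s. The reduction reading gives 28, 32, 36 and 40 m/s.

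**The case against.** The strongest reply is that this is loose wording with little practical effect. Neurophysiologists are among those gathering the data, and the coordinating centre holds meetings before enrolment to make collection uniform. Trained staff may well apply the criterion their laboratory uses, whatever the sentence says. That makes divergence between centres less likely. It does not cure the text: if everyone uses another rule, the protocol misreports the rule and it cannot be replicated from this page.

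The extreme cut-off could also be deliberate, meant to remove only gross slowing. The document neither says so nor rules it out. It fits poorly with a label of merely possible polyneuropathy.

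A further reply is that the enrolment criteria and an exclusion from one analysis are different things, so Study Design and Participants is not strictly contradicted. That is fair. But the ENG/EMG section does not say which analysis it means, so a reader cannot tell whether the patient leaves only the nerve-conduction work or the cohort analysis as well.

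Four stronger readings are tempting, and the document does not support them:
- **That 0.80 × LLN is the intended value.** It is plausible, but no second wording or worked example confirms it.
- **That the cut-off is about 7 to 10 m/s.** This needs limits of 35 to 50 m/s, which are not given.
- **That the rule would almost never fire, or would miss a stated share of cases.** This depends on the velocity distribution in patients with other polyneuropathies, which is not given. Any percentage would follow from the distribution chosen.
- **That misclassified patients would contaminate a neuromyopathy predictor.** The Introduction reports earlier findings on neuromyopathy, and the study plans to test ENG/EMG measures, but no neuromyopathy variable is defined. Nor does any rule say that an unexcluded patient with slow conduction is coded that way. CMAP, SNAP, distal latencies and needle EMG are recorded too.

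**Conclusion.** The point holds as a defect in a stated decision threshold. Literally, the cut-off is one fifth of the lower limit, 4.4 to 16.4 SD below the normative mean for an assumed SD/mean of 0.20 to 0.05. Slowing up to 80% below the limit would go unflagged, and those patients would remain in the neurophysiological analyses. The fourfold gap between the two readings needs no assumption; the SD distances rest on the assumed SD/mean range, and the m/s values on assumed limits.

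The document does not establish which reading is meant, and this review does not judge which is clinically right. No sample-size figure and no definition of the GOS-E outcome is affected. The effect is on who is labelled and who is excluded.

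**What to change.** The sponsor should check the threshold against its laboratory criteria and then:

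1. Correct the ENG/EMG sentence so that it says explicitly whether 20% is a fraction of the lower limit or a reduction below it.
2. Apply that single numeric rule in the data derivation at all four centres.
3. State which analysis the exclusion applies to.
4. Reconcile it with the statement in Study Design and Participants that no further exclusion criteria apply, for instance by separating enrolment criteria from exclusions specific to one analysis.

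The cost is one line of protocol text, a matching line in the analysis plan, and a derivation check. No new data are needed. The downside is that the number of patients flagged may change. It would rise compared with the literal rule if the reduction reading is confirmed, so more patients would leave whichever analysis is named. That makes items 3 and 4 worth settling together with item 1.

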#### Analysis of Genetic Marker

For the subgroup of patients who will sign a further, dedicated informed consent, a blood sample, along with the routine blood drawn at T0, T1, and T2, will be frozen and sent to the University Hospital Neurogenetic Lab of Florence.

Genomic DNA will be obtained from EDTA-whole venous blood samples by Automated Systems QiaCube (Qiagen). The genetic analysis of five different single-nucleotide polymorphisms on APOE and BDNF will be performed by high-resolution melt (HRM) analyses and direct sequencing on automatic genetic analyzer. ApoE genotypes will be investigated by HRM with two sets of PCR primers designed to amplify the regions encompassing rs7412 [NC_000019.9: g.45412079C>T] and rs429358 (NC_000019.9: g.45411941T>C). The samples with known ApoE genotypes, which have been validated by DNA sequencing, will be used as standard references. Analysis of DNA methylation (DNAm) levels of BDNF will be performed according to the following protocol: equal amounts of a genomic DNA sample will be put in four separate tubes into which buffer and the appropriate restriction enzyme combinations added to detect different methylated DNA fractions. The product of a mock digest (Mo) contains all of the input genomic DNA. The product of the methylation-sensitive restriction enzyme mixture (enzyme A) digest (Ms) contains methylated DNA sequences, whereas the product of the methylation-dependent restriction enzyme mixture (enzyme B) digest (Md) contains unmethylated DNA sequences. The product of a double digest (Msd) measures the background and the success of both enzymatic digestions. To analyze the amount of DNA in each digest of each sample and determine the methylation status of CpG islands in gene promoters, all the aliquots will be amplified by a real-time PCR (Rotor-Gene 6000 Corbett Research). The analysis of the BDNF rs6265 will be performed by HRM using the following PCR primers 5′- ACTCTGGAGAGCGTGAATGG-3′ and 5′-ACTACTGAGCATCACCCTGGA-3′. The three genotypes will be identified through sequencing (SEQStudio Automatic Genetic Analyzer Life Technologies). The methylation levels of the gene promoters will be analyzed by the Epitec II DNA Methylation Enzyme Kit (QIAGEN). The genetic polymorphism data will be compared to sex- and age-matched controls of the DNA banking of the neurogenetic laboratory.

### Rehabilitation

The rehabilitation intervention is defined in an ICP based on the International Classification of Functioning, Disability, and Health-World Health Organization (ICF 2001, WHO) model of functioning (32). Synthetically, the standardized rehabilitation assessment and process of care provide, according to the national requirements, at least 3 h per day of specific rehabilitation including physiotherapy, neuropsychological therapy, speech and dysphagia therapy, and occupational therapy. Based on systematic screening at admission, weekly team revisions of the individual rehabilitation plan, and emerging needs during the rehabilitation stay, it is determined the type of aid the patients may need. Additionally, specific training sessions are planned for the patients to be familiar with the prescribed aids. When indicated, psychological support to the patient and/or family is also provided. Physiotherapy may also include robotic rehabilitation of the upper limb according to the individual rehabilitation plan defined by the interdisciplinary team. Specific rehabilitative interventions are summarized in Supplementary Table S2.

### Outcome Measures

The primary outcome is the functional recovery, given by the achievement of a moderate functional disability (GOS-E>4), whereas the independent variables will be the severity of the patients' clinical state at admission. For those patients who will remain in DoC at discharge from the IRU, given that the GOS-E does not allow accurate discrimination between different states of consciousness, consciousness improvement will be considered. The improvement will be stated as the transition from one state of consciousness to a higher one (based on the CRS-R assessment). These outcomes will be measured both at short-term evaluations, T1 and T2, and at long-term ones, T3 and T4.

Secondary outcomes will be considered at the same time points. They are (1) tracheostomy decannulation success and its timing and (2) complete oral feeding recovery corresponding to FOIS score ≥4. Additionally, at follow-up time points (T3 and T4), the level of participation, using the CIQ scale, and the subjective and caregiver perceived QoL, using the QoLibri, will also be considered as secondary outcomes.

